#### Potential moderators

Three organizational factors (workloads, practice environments, and safety organizing) and three personal factors (experience, education, and certification) are proposed moderators. These measures will be obtained on the web-based survey at baseline and the post-intervention assessment. In contrast to our outcomes and potential mediators, the moderators will be obtained from participants and aggregated to the cluster level.

Workloads will be measured by asking participants: 'How many patients did you assume primary responsibility for on your last shift?' For spill reporting, the time referent will be changed to 'the shift the drug spill occurred'. Workload measures correlate significantly with administratively-derived staffing levels and perceived staffing adequacy [28]. Workload is also significantly associated with patient mortality [29], nurse-reported needlesticks [30], and hazardous drug exposure [11].

Practice environments are workplace features that enable nurses to deliver high-quality care [31]. Items from the Practice Environment Scale of the Nursing Work Index, revised for ambulatory oncology, are scored on a 5-point Likert scale, where 1 = *strongly disagree* to 5 = *strongly agree* that the characteristic is present in the practice. The range of setting-level scores on a composite of the 6 subscales was 2.7 (disagree) to 5.0 (strongly agree). Previously analyzed for validity and reliability, acceptable fit was achieved in a structural equation model with a comparative fit index of 0.95 and a root mean-square error of approximation of 0.057, and subscale Cronbach alphas ranged from 0.80 to 0.90 [32]. Our preliminary data show lower scores (that is, poorer practice environments) for nurses who report hazardous drug spills. We will use the mean score of the 23-item composite measure for the proposed analyses (range = 1 to 5).

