The Safety Organizing Scale [22] reflects behaviors employees perform in high-reliability organizations that avert operational failure. Nine items reflect the concept of a safety culture, and importantly, capture observable actions of clinicians. Each item is scored on a 7-point Likert scale (1 = *not at all*, 7 = *to a very great extent*) to reflect the degree to which the nurse and his/her co-workers engage in the behaviors on their work unit. The items identify safe performance as a function of five processes: preoccupation with failure, reluctance to simplify interpretations, sensitivity to operations, commitment to resilience, and deference to expertise. The scale has high internal reliability and discriminant validity [22].

Congruent with prior studies, the three potential moderators described above will be aggregated to the cluster level. In this study, a cluster is considered each of the 11 participating cancer centers. For each cluster, the mean value for these three measures will be calculated from the individual responses from each nurse in the cluster.

Three personal factors will be collected from each participant with the baseline survey: oncology nursing experience (years), education (diploma, associate’s degree, bachelor’s degree, master’s degree, post-master’s degree), and certification (Oncology Nursing Society chemotherapy certification, Oncology Certified Nurse, Advanced Oncology Certified Nurse, other certification).

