Aim 3 will determine whether the treatment intervention effect on PPE use is moderated (strengthened or weakened) by personal (experience, education, certification) and organizational factors (workloads, practice environments, safety organizing). We will use mixed model analyses that include receipt of the treatment intervention, the moderator variables, and the products of treatment intervention receipt with the moderator variables as predictors of PPE use. Significance tests of the product terms between moderator and intervention variables will indicate whether moderation is present [38]. We hypothesize that at least one of these moderator variables will interact significantly with the treatment intervention. When the product term is significant, we will conduct a *post hoc* analysis by plotting the PPE use versus intervention at various levels of the moderator variables. Using graphical presentations, we can show the size of the intervention effect and how the effects vary based on the values of moderate variables.

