#### Sample size considerations and statistical power

The design and sample size for this study were determined in part by power analysis conducted by Optimal Design software [39] that is designed specifically for mixed models such as ours in which nurses are nested within sites that are treated as a random factor. We considered power for detecting a medium sized effect of the intervention and a medium sized multiple correlation (both as defined by Cohen) [40]. We considered scenarios with different numbers of clusters/sites, with different average numbers of nurses per site, and with different levels of the intraclass correlation coefficient (ICC) ranging from 0.01 to 0.03. The ICC will be a measure of the extent that PPE use differs across sites. The higher the ICC, the greater the sample size needed. ICCs of up to 0.03 are common; therefore, we aimed to obtain 80% power for tests with a 2-tailed alpha of 0.05 to detect medium sized effects with this ICC. Analysis revealed that we will obtain this power if our sample includes 11 sites with a mean of 26 participating nurses. In reality, our sites have a mean of 35 nurses (range of 20 to 90), suggesting that we will achieve 80% power even if we have a 25% decrease in the expected sample size (n = 287).

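### Aim 3 describes a display of moderated effect size only for product terms that reach significance, so the displayed differences between moderator levels are biased away from zero when the true interaction is small

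*Protocol article*

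**What the plan says.** The Potential moderators section names six factors: "Three organizational factors (workloads, practice environments, and safety organizing) and three personal factors (experience, education, and certification) are proposed moderators". The three organizational ones are site means: "the three potential moderators described above will be aggregated to the cluster level. In this study, a cluster is considered each of the 11 participating" centers.

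For Aim 3, the Statistical analysis section fits mixed models that contain treatment receipt, "the moderator variables, and the products of treatment intervention receipt with the moderator variables as predictors of PPE use". Three statements follow:

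- The criterion: "Significance tests of the product terms between moderator and intervention variables will indicate whether moderation is present".
- The condition for showing anything further: "When the product term is significant, we will conduct" a post hoc step, in which PPE use is plotted against intervention at several moderator values.
- The purpose of those plots: "Using graphical presentations, we can show the size of the intervention effect and how the effects vary based on the values of moderate variables".

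On Aim 2 the same section defines an estimate of the mediated effect and says that a 95% confidence interval will be calculated for it, with no significance condition. Aim 3 has no matching sentence.

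No significance level is given for Aim 3. The sample-size section gives one for the power analysis: "we aimed to obtain 80% power for tests with a 2-tailed alpha of 0.05 to detect medium sized effects with this ICC".

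**The concern.** Aim 3 asks how far personal and organizational factors strengthen or weaken the intervention effect. That is a question about size. The rule in the article answers it with a test, and shows size only where the test succeeds.

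Two things follow if the rule is applied as written and nothing is added. First, an estimate shown because it passed a threshold is, on average, further from zero than the true value. This happens with a single moderator, so it is not a multiplicity problem, and a stricter threshold makes it larger. Second, a factor that misses the threshold is easily read as not moderating the effect, although its interval may include a large interaction. The organizational factors are the most exposed, because their information comes from 11 sites.

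The results are meant to inform nurses, administrators and policymakers. Sizes of moderation that are overstated, or left out because power was low, would serve them poorly.

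**Working it through.** **Inputs from the article.** 11 sites; 382 nurses expected, mean 35 per site; 287 nurses after a 25% loss; mean 26 per site in the power statement; ICC up to 0.03; two-tailed alpha 0.05; 80% power for a medium effect.

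**Assumptions.** Medium is read as 0.5 SD. The 5% two-sided level is carried over to Aim 3. The article gives no interaction size, so true values of 0.1, 0.2, 0.3 and 0.5 outcome SD per moderator SD are used. Arms are balanced, moderators are standardised and tested one at a time, and estimates are unbiased before selection. Personal factors are treated as nurse-level.

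**Step 1: the article's own figure.** With J sites of n nurses, SE² = (4/J)(ICC + (1 − ICC)/n). For J = 11, n = 26, ICC = 0.03: SE² = 0.3636 × (0.03 + 0.0373) = 0.0245, so SE = 0.156. With d = 0.5 and a noncentral t on 9 df, power is 0.811 (0.808 with a 5/6 split of sites). The stated 80% is reproduced.

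**Step 2: standard errors of a product term.**

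- Nurse level: SE = 2√0.97/√N. This is 0.101 SD for N = 382 and 0.116 SD for N = 287.
- Site level: SE = √[(4/11)(0.03 + 0.97/n)]. This is 0.145 SD for n = 35 and 0.156 SD for n = 26. The test has 7 df (11 sites less 4 site-level coefficients).

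The smallest estimate that would be displayed is therefore about 1.96 × 0.101 = 0.20 SD at nurse level with 382 nurses. At site level with 35 nurses per site it is about 2.365 × 0.145 = 0.34 SD. The site-level value is approximate, because the estimated SE varies on 7 df.

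**Step 3: mean size among significant estimates.** One case by hand: nurse level, N = 382, true value 0.20, SE = 0.1008. The threshold is 1.96 × 0.1008 = 0.1976, which is 0.024 SE below the truth, so power is about 0.51. The mean of a normal estimate above the threshold is 0.20 + 0.1008 × 0.399/0.51 = 0.279, which is 1.4 times the truth. The wrong tail is negligible.

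The full set comes from 1,000,000 simulated estimates per case. Each cell gives power, then the mean absolute significant estimate divided by the truth:

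| True interaction (SD) | Nurse level, N = 382 | Nurse level, N = 287 | Site level, n = 35 | Site level, n = 26 |
|---|---|---|---|---|
| 0.1 | 17%, 2.5 | 14%, 2.9 | 9%, 3.3 | 9%, 3.5 |
| 0.2 | 51%, 1.4 | 41%, 1.6 | 22%, 1.8 | 20%, 1.9 |
| 0.3 | 85%, 1.1 | 73%, 1.2 | 43%, 1.4 | 38%, 1.4 |
| 0.5 | about 100%, 1.0 | 99%, 1.0 | 84%, 1.1 | 78%, 1.1 |

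Without selection on the p-value the expected ratio is 1.0 in every cell.

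**Step 4: what the factors apply to.** The effect plotted at moderator value m is (treatment coefficient) + (product coefficient) × m. The inflation is in the product coefficient, hence in the difference between moderator levels. For a centred moderator, the effect at its mean (m = 0) does not involve the product term.

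**Limits.** The nurse-level figures fit years of experience directly. Education (five categories) and certification (four types) may need several product terms each. Fitting the three organizational moderators and their products together would use 8 site-level coefficients, leave about 11 − 8 = 3 df and lower power further.

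**The case against.** The strongest reply is that testing an interaction and then plotting it at chosen levels is a common way to interpret moderation. The article calls the step post hoc and does not say that plots are the only source of estimates. If all coefficients are tabulated, choosing which to plot biases none of them, and the content of tables is commonly left to an analysis plan.

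Much of this stands, and it rules out several stronger readings that a reader might infer:

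- *That moderators missing significance get no estimate.* The models contain every product term and each is tested, so each has a coefficient and a standard error. Only the plot is withheld.
- *That their coefficients will go unreported.* The article does not say so. It is silent on which coefficients will be tabulated.
- *That the displayed sizes will be inflated by some definite amount.* No interaction size is given, and at 0.5 SD the inflation is 0 to 1% at nurse level and 7 to 10% at site level.
- *That the intervention effect itself is overstated by these factors.* They apply to differences between moderator levels.

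The reply does not remove the point. The condition on significance is written into the article rather than left open, it governs the only display of size described for Aim 3, and significance is also the sole stated criterion for moderation.

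**Conclusion.** The point holds in a limited form. The article ties the only described display of moderated effect size to a significant product term, and promises no interval for moderators that miss it. Differences between moderator levels shown under that rule, taken alone, are biased away from zero.

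For assumed true interactions of 0.1 to 0.5 SD, the bias runs from about 2.5 times to none for a nurse-level moderator with 382 nurses, and from about 3.3 to 1.1 times for a site-level moderator with 35 nurses per site. Power for an assumed 0.2 SD interaction is only about 20 to 22% at site level. A real organizational moderator of that size would usually go undisplayed and, when displayed, would average about 1.8 to 1.9 times its true size.

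These figures rest on the assumed interaction sizes, a 5% two-sided test, and one standardised moderator at a time. The primary comparison, its test and the sample size are unaffected. This is a free improvement to a secondary aim.

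**What to change.** In the Aim 3 paragraph of the Statistical analysis section:

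1. Delete the clause that makes the plots conditional on a significant product term.
2. State that the interaction estimate, or estimates for a factor with several categories, will be reported with 95% confidence intervals for all six moderators whatever the p-value.
3. State that plots will not be selected on significance. They will show the intervention effect with a confidence band at pre-set moderator values (for example the 25th, 50th and 75th percentiles) or for each category.
4. Keep the p-value as the test only, and describe a non-significant term by its interval rather than as no moderation.

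The cost is about one sentence of text and a few more estimates and plots from models already planned. It needs no new data and changes no test or sample size.

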#### Sample size considerations and statistical power

The design and sample size for this study were determined in part by power analysis conducted by Optimal Design software [39] that is designed specifically for mixed models such as ours in which nurses are nested within sites that are treated as a random factor. We considered power for detecting a medium sized effect of the intervention and a medium sized multiple correlation (both as defined by Cohen) [40]. We considered scenarios with different numbers of clusters/sites, with different average numbers of nurses per site, and with different levels of the intraclass correlation coefficient (ICC) ranging from 0.01 to 0.03. The ICC will be a measure of the extent that PPE use differs across sites. The higher the ICC, the greater the sample size needed. ICCs of up to 0.03 are common; therefore, we aimed to obtain 80% power for tests with a 2-tailed alpha of 0.05 to detect medium sized effects with this ICC. Analysis revealed that we will obtain this power if our sample includes 11 sites with a mean of 26 participating nurses. In reality, our sites have a mean of 35 nurses (range of 20 to 90), suggesting that we will achieve 80% power even if we have a 25% decrease in the expected sample size (n = 287).

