### Setting and sample

#### Settings

Site inclusion criteria are ambulatory oncology infusion settings with at least 20 employees who meet the eligibility criteria listed below. In addition, the chief nursing executive for cancer services in each facility provided endorsement of the study. Exclusion criteria are infusion areas that are not within easy access to the on-site study coordinator’s office or lack on-site phlebotomy services.

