### Statistical analysis

Survey data will be stored on the password-protected, user-authenticated encrypted server behind a firewall. Our hypotheses are focused on the efficacy of an audit and feedback intervention to nurse participants. A total of 382 nurses are expected to be sampled from 11 sites. Each site is randomized into either control or intervention condition. Because the nurses within the same site are likely to show correlated outcomes, we will use linear mixed-effects models to account for the intraclass correlation for the proposed cluster randomized trial [36,37]. More specifically, we will use a random intercept model in which a variable *site* is created to identify the sites, and then adding *site* as a random effect to the mixed model.

Aim 1 evaluates the efficacy of audit and feedback to improve recommended PPE use (compared with an educational video). The outcome variable of the fixed-effect structure is the PPE use scores. The predictor of the fixed effect is the intervention indicator variable. The data from the PPE use questionnaire and demographics variables that are included in the fixed-effect structure to increase the precision of estimates. The random effect in the model is the *site* variable. We assume the *site* variable follows a normal distribution with mean zero and is independent of the error term in the mixed model. The hypothesis is that there will be a significant intervention effect such that nurses in sites receiving the treatment, in addition to the web-based educational module, will report higher PPE use scores compared to nurses in sites randomized to receive only the control. Means within time will be computed as descriptive statistics to help describe the effect.

Aim 2 will determine whether knowledge about PPE use and perceived risk of drug exposure mediate the effect of the treatment intervention on PPE use. The hypothesis is that the effect of the treatment on PPE use will be at least partially mediated by knowledge and perceived risk. To measure the mediation effect, we fit two linear mixed models. The first model is the same model we use in Aim 1. The second model adds the two potential mediators in the first model. The mediator effect is measured as the difference in the coefficients of the intervention variable between the two models. A 95% confidence interval is calculated for the estimate. If the confidence interval does not cross zero, it shows that mediation effect is statistically significant.

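### The claim of 80% power at 287 nurses holds only for equal site sizes; with sites of 20 to 90, unadjusted power is about 76-79% and the tolerable loss about 11-22%, not 25%.

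*Protocol article*

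**What the plan says.** The section on sample size and power gives the target: "we aimed to obtain 80% power for tests with a 2-tailed alpha of 0.05 to detect medium sized effects with this ICC", the ICC being 0.03. The effect is given in words only: "We considered power for detecting a medium sized effect of the intervention and a medium sized multiple correlation (both as defined by Cohen"). The design result is that "we will obtain this power if our sample includes 11 sites with a mean of 26 participating nurses". The article then turns to the actual sites: "our sites have a mean of 35 nurses (range of 20 to 90"), and concludes from this, "suggesting that we will achieve 80% power even if we have a 25% decrease in the expected sample size (n = 287").

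The statistical analysis section supplies the total: "A total of 382 nurses are expected to be sampled from 11 sites". The same section plans a linear mixed model with site as a random intercept, adjusted for PPE questionnaire data and demographics to gain precision. The randomization section acknowledges that sites differ in size and allocates them in blocks of two after ordering by size. The power section varies the number of sites, the average site size and the ICC, but mentions no allowance for variation in size between sites.

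**The concern.** In a cluster trial analysed with a site random effect, a large site adds little information beyond a certain size, because the between-site variance does not shrink with more nurses. A fixed total spread unevenly therefore carries less information than the same total spread evenly. The article moves from a required mean of 26 to an available mean of 35 and treats the difference as a 25% reserve. In the same sentence it reports a more than fourfold range in site size.

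At stake is a specific statement in the protocol: how many nurses can be lost before power falls below 80%. If that figure is too generous, recruitment and retention may be judged adequate when they are not, and a null result may be read against a power somewhat higher than the trial had.

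A second question is what the 25% is taken from. The article sets what the sites have (35) against what must participate (26), and the lower end of the range equals the site entry criterion of "at least 20 employees who meet the eligibility criteria listed below".

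**Working it through.** **Inputs from the article:** 11 sites; two-sided alpha 0.05; ICC ρ = 0.03; required mean 26; total 382; smallest site 20, largest 90; size-ordered blocks of two, which split 11 sites 6:5.

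**Assumptions:** d = 0.5 SD for a medium effect; every site loses the same 25%; no covariate gain; individual site sizes bounded as in step 3.

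**1. The article's own figure.** For a common size n, power comes from a noncentral F test with 1 and 11 − 2 = 9 df and noncentrality

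λ = 11 d² / [4(ρ + (1 − ρ)/n)].

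With n = 26: λ = 11 × 0.25 / [4 × (0.03 + 0.97/26)] = 10.21, power 81.1%. The exact 6:5 split gives 80.8%. The stated 80% reproduces, with equal sites and no covariates.

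**2. The totals.** 382/11 = 34.7; 382 × 0.75 = 286.5, given as 287; 11 × 26 = 286. These agree.

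**3. Possible site sizes.** Total 382, minimum 20 and maximum 90 bound the spread:
- least varied: 90, 20 and nine of about 30.2 (coefficient of variation 0.51)
- graded example: 90, 55, 42, 35, 30, 27, 23, 20, 20, 20, 20
- most varied: 90, 90, 42 and eight of 20 (coefficient of variation 0.77)

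**4. Power with unequal sites.** In the mixed model a site of size m contributes information 1/(ρ + (1 − ρ)/m). With arm totals A and B, λ = d²/(1/A + 1/B). I averaged power over all allocations that the size-ordered blocks allow.

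*Least varied, shrunk by 25%* (67.5, 15, nine of 22.67): contributions 22.54, 10.56 and 13.74. The arm holding the largest site has 22.54 + 4 × 13.74 = 77.49; the other has 5 × 13.74 = 68.69. The unpaired smallest site adds 10.56 to one of them, giving λ = 9.65 or 9.79. Power is 78.9-79.5%, mean 79.2%.

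*Most varied, shrunk by 25%* (67.5, 67.5, 31.5, eight of 15): contributions 22.54, 22.54, 16.45 and 10.56. Arm totals before the unpaired site are 22.54 + 16.45 + 3 × 10.56 = 70.68 and 22.54 + 4 × 10.56 = 64.79 (rounded contributions). λ = 9.01 or 9.12. Power is 76.2-76.7%, mean 76.4%.

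| Site sizes | Power at 287 | Power at 382 | Nurses for 80% | Tolerable decrease from 382 |
|---|---|---|---|---|
| Least varied | 79.2% | 84.8% | about 298 | 22% |
| Graded | 78.3% | 84.0% | about 310 | 19% |
| Most varied | 76.4% | 82.3% | about 340 | 11% |

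**5. Detectable effect at 287.** 80% power at 9 df needs λ = 9.92. Since λ scales with d², the detectable effect is 0.5 × √(9.92/λ). At the mean λ this is 0.5 × √(9.92/9.72) = 0.505 for the least varied sizes and 0.5 × √(9.92/9.06) = 0.523 for the most varied: about 0.51 to 0.52 SD instead of 0.50.

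**6. Covariate adjustment.** Replacing (1 − ρ) by (1 − ρ)(1 − R²) within sites, R² = 0.05 gives 80.3% for the least varied sizes, and R² = 0.16 gives 80.1% for the most varied.

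**7. Smaller ICC.** At ρ = 0.02, also within the range that the article considered, the unequal sites give 82.6-84.9% at 287.

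**The case against.** The strongest reply is that nothing has been miscalculated. The stated 80% reproduces, a common cluster size is an ordinary planning simplification, and the shortfall is 1 to 4 points at the largest ICC considered. All of that stands. The point concerns an assumption that the article's own range contradicts, not faulty arithmetic.

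The planned analysis is also adjusted, and a modest within-site R² would bring power back to 80%. This stands too, so 76-79% must be labelled an unadjusted figure. But the article states no R², and its 80% already reproduces without any covariate gain. If adjustment is the hidden reserve, the text should say so.

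Three stronger readings are tempting, and the documents do not support them:
- *There is no safety margin.* Not so: power at 382 is 82-85%, and a decrease of 11-22% is tolerable.
- *Power is below 80% however the loss falls.* The article fixes no pattern of loss. If it falls mainly on the largest site (50, 20 and nine of about 24, same total), power is 80.2%. Only under proportional loss does every permitted set of sizes fall short.
- *The 382 is the full eligible staff.* This is a reasonable inference from the contrast between nurses whom sites have and nurses who participate, and from the minimum of 20. But the article calls 382 the expected sample, and the 76-79% does not depend on the answer. If it is the roster, the allowance must also absorb nurses who never enrol; no participation rate is given from which to size that.

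**Conclusion.** The point holds in a limited form. On the article's inputs, 80% power at 287 nurses is an equal-site figure. With the stated total and range, unadjusted power at 287 is about 76-79%, and the decrease that keeps 80% is about 11-22% rather than 25%. This rests on d = 0.5 for a medium effect, ICC 0.03, proportional loss across sites, no covariate gain, and site sizes bounded by the stated minimum, maximum and total.

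The reserve is overstated, not missing. Covariate adjustment, a lower ICC or loss concentrated in the largest site could each bring power to 80% or above at 287. The consequence is modest: the detectable effect moves from 0.50 to about 0.51-0.52 SD. It merits correction because the article names a precise tolerance that its own figures do not bear out.

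**What to change.** In the sample size section:

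1. Either state that, with sites of 20 to 90 and no covariate adjustment, 287 nurses give about 76-79% power for 0.5 SD at ICC 0.03, and that the tolerable decrease from 382 is about 11-22%; or keep 80% at 287 and state the covariate R² relied on.
2. Give the effect size as a number.
3. Say whether 382 is the eligible roster or the expected enrolment, and so whether the allowance covers non-enrolment as well as loss by the 18-month endpoint.
4. Recompute with the actual enrolled site sizes. Randomization follows enrolment and the baseline survey, so these are known before allocation; only the later pattern of loss must be assumed.

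The cost is a few sentences, one short recalculation and a slightly less favourable stated power. No nurses or sites need to be added.
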